**INTRODUCTION**

Greater trochanter pain syndrome (GTPS) is a broad term used to define pain and tenderness in the greater trochanter region of the femur^1,2^. It is estimated that 10 to 25% of the population will develop some type of pain in the lateral region of the hip^1–3^, predominantly in women over 40 years old ^2–6^. The GTPS directly impacts the worsening of quality of life, which is similar to the findings in individuals with severe hip osteoarthritis^7^. Women have mechanisms that can influence the onset of GTPS, such as smaller gluteal tendon insertions in the femur, shorter gluteal moment arm and gluteus medius weakness^6^.

Changes in the function of the gluteus medius and minimus muscles can lead to poor hip and pelvic control and lead to increased hip adduction in the frontal plane, especially in unilateral support positions, such as in gait^6,8^. The literature indicates that active treatments, those in which participants perform physical exercises, are preferable to passive approaches in the treatment of GTPS. Active treatments result in better results in the short^9,10^, medium^9^and long term^9-11^in terms of pain and function when compared to rest, shock wave therapy and/or invasive treatments, eg, injection. corticosteroid^5,9,11^. Surgical interventions are generally reserved for recalcitrant cases^1,2,5,12^.

Despite previous knowledge that physical exercise generates benefits for GTPS and chronic pain in general, no study has attempted to demonstrate the efficacy of motor control exercise for GTPS. Individuals with GTPS have abnormal control of lower limb movements and deficient neuromuscular parameters^8,13,14^and alterations in the trunk and pelvic kinematics during walking^15^, however, no study used neuromuscular training as a treatment strategy and there is insufficient evidence about the influence of this intervention on the clinical and biomechanical aspects of these participants. Thus, this study aims to compare the effect of a general exercise protocol versus a motor control training program on the onset and after treatment at 8 and 60 weeks in women with GTPS.

Our hypothesis is that both women undergoing the motor control protocol and women undergoing the general exercise protocol will show improvements in all outcomes evaluated, although the motor control group is superior because the intervention is specific to the hip region.

**MATERIALS AND METHODS**

This is a randomized controlled trial, blind to evaluator and statistician, with 2 arms, registered in the Brazilian Registry of Clinical Trials (RBR-37gw2x) and has a Universal Trial Number (U1111-1234-0705)

**Ethical approval and consent**

The study was approved by the Research Ethics Committee of the Faculty of Philosophy and Sciences, São Paulo State University (UNESP) , Campus of Marília (CAAE: 87372318.1.0000.5406). All participants will sign an informed consent form.

**Participants**

**Recruitment**

Women with GTPS will be recruited from the community, universities and within the public health service, through digital means (facebook and instagram) and written dissemination (flyers). Interested participants will contact the principal investigator by phone or social media.

**Clinical screening**

**Screening by phone**

Initial screening will be done by phone. Potential participants will be eligible for the study if they are between 18 and 70 years old, do not engage in regular physical activity (Tegner activity level ≤4) ^16^and have had lateral hip pain for ≥ 3 months. They should have pain during one or more of the seven daily activities: walking, standing for a long period, getting up from a sitting position, sitting for a long time, going up and down stairs, going up and down hills and lying down. side. Potential participants will be ineligible for the study if they have a body mass index (BMI) > 36 kg/m2, have received some type of invasive intervention for lateral hip pain or physical therapy intervention for hip pain in the past 12 weeks, have morning hip stiffness ≤ 60 minutes, any disease that affects the neuromuscular system or that may prevent data collection, has had spine or hip surgery, any infectious condition, any neoplasm, or cannot commit to participate during treatment^10-12,15,17^.

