**Physiotherapeutic evaluation**

Potential participants who meet the eligibility criteria over the phone will undergo two assessments. The first will be held to screen for inclusion and exclusion criteria that were not possible to assess by phone, as well as explain in more detail the nature of the study and the commitment required, with an opportunity for participants to ask questions, and the second will be carried out by a blind evaluator to assess outcomes. The physical therapy evaluation will be carried out at São Paulo State University and will take about 40 minutes to 1 hour. The assessment will be done by a physical therapist with 8 years of experience, with a master's degree in the area of ​​musculoskeletal disorders. Demographic data will be collected, including age, weight, height, BMI, etc. It will be determined whether the participants have the ability to manipulate shoes and socks^18^, have limited range of motion of the spine, hips or lower limbs that affect gait or data collection, or a visible discrepancy in the lower limbs. It will be evaluated whether the participants have sensitivity to palpation over the greater trochanter region of the femur^8,19,20^. If both hips are symptomatic, the more painful side will be evaluated ^10^. The Trendelenburg sign, which is the pelvic drop during unipodal support, indicating inefficiency of the hip abductor muscles, will be evaluated^5,8,19^.

The tests that will be used for clinical evaluation aim to define the exact location of the pain and transmit compressive and/or tension forces in the tendons of the hip abductor muscles on the greater trochanter. Participants must experience pain over the greater trochanter of the femur in ≥ two of the seven provocative clinical trials for pain^12,14,17^. They are:

• Greater trochanter palpation: positive palpation sensitivity, considered when there is pain over the greater trochanter of the femur, during assessment in lateral decubitus (LD) with the pain side up, flexion of the hip joint and knees together^5,6,8.11.17^. This test has been reported to have a sensitivity of 85.7% and a specificity of 61.1%^6^.

• FADER: Participants in dorsal decubitus (DD) should report pain over the greater trochanter when the affected lower limb is positioned in 90º flexion, adduction and external rotation of the hip^17^.

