GTPS is, by definition, a painful syndrome, therefore, the specific cause of pain may be difficult to define, as more than one pathology can present similar symptoms in the hip region^5,6,17,19^. We will apply a combination of multiple clinical tests to avoid including participants who do not have GTPS, eg hip osteoarthritis^17,19^. The diagnosis of GTPS is clinical and two studies by Grimaldi et al. 2017 and Ganderton et al. 2017 demonstrated that palpation over the greater trochanter has a sensitivity of 80% and 85.7%, respectively, and a specificity of 47% and 61.1%, respectively. They also reported likelihood ratios of 0.43 and 2.2, respectively, demonstrating that this test alone, when negative, is able to rule out the presence of GTPS^6,19^. However, the combination of palpation and one of the other tests, FABER, Single leg stance for 30 seconds , FADER, FADER-R, ADD, ADD-R increases the chances of detecting GTPS due to the specificity of these tests, which can reach 100%^19^.

In order to maintain methodological quality, this clinical trial will comply with the standards of the consort group^30^. Study participants will be randomized to join one of the groups through the concealed allocation^17.30^. Due to the nature of the intervention, it is not possible to blind the clinician or participant to group allocation. Only the assessor of outcome measures and the statistician are able to be blinded to treatment allocation. The importance of not revealing anything to the assessor about the nature of the treatment will be strongly emphasized to participants. Statistical analysis will be conducted blind to treatment group allocation - actual groups will only be revealed after analysis. In addition, intention-to-treat analysis will be used, which preserves the study's randomization and simulates the real-life situation^31^. As a limitation of the study, we highlight the participation of women only, so care must be taken when extrapolating data to men with the same conditions.

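### The morning-stiffness exclusion rules out brief stiffness, lets stiffness over 60 minutes through, and leaves women with no stiffness undefined

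*Protocol*

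**What the plan says.** The Screening by phone section has two parts. The first gives the conditions for entry: age, activity level, duration of lateral hip pain, and pain in a listed daily activity. The second is a list of grounds for ineligibility, which opens: "Potential participants will be ineligible for the study if they have a body mass index (BMI) > 36 kg/m2". Within that second list, among items joined by commas and a closing 'or', a candidate is ineligible if she is found to "have morning hip stiffness ≤ 60 minutes".

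The Physiotherapeutic evaluation section then describes a first in-person visit, held to "screen for inclusion and exclusion criteria that were not possible to assess by phone". It does not mention stiffness. The Discussion gives the diagnostic aim: "We will apply a combination of multiple clinical tests to avoid including participants who do not have GTPS, eg hip osteoarthritis". It does not mention stiffness either. The phone-screening item is the only reference to morning stiffness in the protocol.

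**The concern.** An exclusion with an upper bound removes the low end of the scale and keeps the high end. Here short stiffness disqualifies and long stiffness does not. No reason is given, and the other numeric exclusion in the same sentence works the opposite way, removing high values of body mass index.

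The item is asked of every candidate by phone, before any examination. If screeners follow it exactly, it shapes the enrolled sample in a way the protocol does not justify. If they apply what they think was meant, two screeners can reach opposite decisions on the same woman, and some enrolled women will not meet the criteria as written. In both cases a reader of the results could not tell from the protocol who was eligible.

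**Working it through.** No power, error-rate or sample-size formula applies. The check is a literal application of the rule, followed by a search of the protocol for anything that changes its meaning.

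**Step 1: which list the item is in.** It follows the clause that opens the ineligibility list, so it excludes. Each item in that list is a sufficient ground by itself, and no wording ties stiffness to a second sign.

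**Step 2: apply the rule.** Let s be the duration of morning hip stiffness in minutes. The rule is: ineligible if s ≤ 60. The complement, not excluded by this item, is s > 60. The values of s below are illustrative.

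| s (minutes) | Absence counted as 0 minutes | Item requires some stiffness to be present |
|---|---|---|
| none | excluded (0 ≤ 60) | not excluded |
| 10 | excluded | excluded |
| 60 | excluded | excluded |
| 61 | not excluded | not excluded |
| 120 | not excluded | not excluded |

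The two readings differ only in the first row. Under both, brief stiffness excludes and prolonged stiffness does not.

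**Step 3: compare with the neighbouring threshold.** The other numeric exclusion is "body mass index (BMI) > 36 kg/m2", which removes the high end. The stiffness item removes the low end. The contrast does not prove an error, but it shows that the direction cannot be taken as a convention of the list.

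**Step 4: look for a correction.**
- Physiotherapeutic evaluation: this visit covers criteria that could not be settled by phone. It includes a check on managing shoes and socks and on limited movement of the spine, hips or lower limbs. These could belong to a joint-disease rule, but the text does not connect them with stiffness.
- Discussion: the aim is to "avoid including participants who do not have GTPS, eg hip osteoarthritis", to be met by combining clinical tests. Stiffness duration is not among those tests, and nothing says how excluding only brief stiffness would serve the aim.

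**Step 5: what the item does not touch.**
- Sample size: the stated inputs are power 0.80, alpha 0.05, effect size 0.5 and 15% dropout, giving 60 women. None depends on stiffness.
- Comparison of arms: under Randomization, allocation and blinding, women are allocated only after meeting all eligibility criteria. Both arms pass the same screen.

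**The case against.** The strongest reply is that the intended direction is not documented. The protocol never states the purpose of the item, and the exclusion sentence ends with a group of citations that may hold a composite definition in which the sign is deliberate. This stands. It is a good reason not to assert that the inequality must simply be reversed. It does not rescue the text: if the item is one component of a larger rule, the protocol has made that component a sufficient exclusion and has not linked the others to it.

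Three stronger readings are tempting, and the documents do not support them.

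- A reader might infer that only women with prolonged stiffness can enter. That holds only if absence of stiffness is counted as 0 minutes. In ordinary usage a woman with none does not have stiffness of any duration and would stay eligible. The protocol does not settle this.
- A reader might infer that most of the intended population is removed. The protocol gives no distribution of stiffness, so any share or count of callers would be a guess.
- A reader might infer that the enrolled women would not have GTPS, or that the difference in pain between arms would be diluted. Every participant still needs at least three months of lateral hip pain, pain in a listed daily activity, and trochanteric pain on at least two of seven provocation tests. No loss of contrast can be derived from the text.

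**Conclusion.** The point holds as a defect in one stated entry criterion. Brief morning stiffness excludes, stiffness beyond 60 minutes does not, and the handling of women with none is unclear. The item is either mis-signed or an incomplete piece of a composite rule, and the documents do not show which.

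The consequence is limited to the make-up of the sample and the reproducibility of screening. It does not bias the randomized comparison or alter the sample-size calculation. Its numerical size is unknown, because it depends on how many candidates have stiffness of up to 60 minutes. The conclusion rests on two things: a literal reading of the list, and the absence of any other mention of stiffness in the protocol. It is worth correcting because the item is a working gate for every candidate and nothing in the document resolves it.

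**What to change.** The sponsor should reconcile the criterion with the intended population, in three parts.

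1. Confirm the intended direction of the inequality. If the item belongs to a composite joint-disease rule, write that rule out in full so that stiffness alone does not exclude. The choice is the sponsor's, and the documents do not allow it to be made here.
2. State how a woman with no morning stiffness is classified.
3. Re-check the screening log for women already accepted or refused under the present wording, and record which interpretation the screeners used.

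The cost is an amendment of about one line, or a few lines for a composite rule, and a look back through the log. The analysis and the sample size need no change.

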**Physiotherapeutic evaluation**

Potential participants who meet the eligibility criteria over the phone will undergo two assessments. The first will be held to screen for inclusion and exclusion criteria that were not possible to assess by phone, as well as explain in more detail the nature of the study and the commitment required, with an opportunity for participants to ask questions, and the second will be carried out by a blind evaluator to assess outcomes. The physical therapy evaluation will be carried out at São Paulo State University and will take about 40 minutes to 1 hour. The assessment will be done by a physical therapist with 8 years of experience, with a master's degree in the area of ​​musculoskeletal disorders. Demographic data will be collected, including age, weight, height, BMI, etc. It will be determined whether the participants have the ability to manipulate shoes and socks^18^, have limited range of motion of the spine, hips or lower limbs that affect gait or data collection, or a visible discrepancy in the lower limbs. It will be evaluated whether the participants have sensitivity to palpation over the greater trochanter region of the femur^8,19,20^. If both hips are symptomatic, the more painful side will be evaluated ^10^. The Trendelenburg sign, which is the pelvic drop during unipodal support, indicating inefficiency of the hip abductor muscles, will be evaluated^5,8,19^.

The tests that will be used for clinical evaluation aim to define the exact location of the pain and transmit compressive and/or tension forces in the tendons of the hip abductor muscles on the greater trochanter. Participants must experience pain over the greater trochanter of the femur in ≥ two of the seven provocative clinical trials for pain^12,14,17^. They are:

• Greater trochanter palpation: positive palpation sensitivity, considered when there is pain over the greater trochanter of the femur, during assessment in lateral decubitus (LD) with the pain side up, flexion of the hip joint and knees together^5,6,8.11.17^. This test has been reported to have a sensitivity of 85.7% and a specificity of 61.1%^6^.

• FADER: Participants in dorsal decubitus (DD) should report pain over the greater trochanter when the affected lower limb is positioned in 90º flexion, adduction and external rotation of the hip^17^.

• FADER-R with static muscle test: Participants in DD, have to report pain when the affected lower limb is positioned in the same way, but maintaining isometric resistance to internal rotation at the end of the range of motion^5,6,8,11,17^. This test is a modification of the resisted external rotation test, which has been reported to have 42.3% sensitivity and 95% specificity^6^.

• FABER: Participants in DD should report pain when the affected lower limb is positioned in flexion, abduction and external rotation of the hip^6,17,18^. This test has been reported to have a sensitivity of 50% and a specificity of 83%^18^.

• ADD: Participants must report pain when the affected lower limb is positioned in passive hip adduction in LD^17^.

• ADD R: Participants must report pain when the affected lower limb is positioned in passive hip adduction in LD, but maintaining isometric resistance in abduction^17^. This test has been reported to have a sensitivity of 50% and a specificity of 97.3%^6^.

• Single leg Positioning: The participants should report pain to lean on one leg for 30 seconds. This test has a sensitivity of 45.4% and a specificity of 84.2% to indicate SDTM^6^.

**Sample size and power analysis**

Sample calculation was performed using the G * Power software, based on the measure of the level of pain, as it is the primary outcome of the research. A power of 0.80, error probability α 0.05, effect size of 0.5 and dropout rate of 15% were used, for this we will recruit 60 participants (30 in each group)^9^.

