**Statistical analysis**

The study will be run as a superiority trial. The statistical analysis will follow the intention-to-treat concept. Statistical analysis will be performed using the software IBM SPSS Statistics for Windows, version 20.0 (IBM Corp., Armonk, N.Y., USA) and statistician will be blind. Data will be evaluated using exploratory statistical techniques. Firstly, the normality and homogeneity of the data will be verified and then the appropriate statistical analyses will be adopted for the variables. The between-group differences and their respective confidence intervals at 95% will be calculated by constructing mixed linear models interaction of group data versus time. The linear mixed-effect model will be applied to the primary and secondary outcomes. “Time” and “group” will be considered fixed effects, whereas the participants will be considered random effect. The dependent variable baseline values will be included as a covariate for the correction of possible baseline between-group differences.

A causal mediation analysis will be conducted using the “mediate” package in R (The R Foundation for Statistical Computing). A model-based inference approach will be used to estimate the average causal mediation effect (ACME), average direct effect (ADE) and the average total effect^29^.

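### The stated 80% power at effect size 0.5 does not follow: 60 women with 15% dropout give about 42% power, and 60 suits an effect of about 0.8

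*Protocol*

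**What the plan says.** The Protocol, under Sample size and power analysis, bases a G*Power calculation on pain level, the primary outcome. It takes a power of 0.80 and "error probability α 0.05", and gives the other inputs and the resulting number as "effect size of 0.5 and dropout rate of 15% were used, for this we will recruit 60 participants (30 in each group". It does not name the test, the sidedness, the type of effect size, a standard deviation or a correlation.

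Under Primary outcome there is a single primary measure, average pain over the previous week on a 100 mm VAS. Week 8 is the main time point and week 60 is secondary. Under Statistical analysis, "The study will be run as a superiority trial", and "The between-group differences and their respective confidence intervals at 95% will be calculated" from a linear mixed model with group, time and the baseline value. The sample size section makes no use of that baseline adjustment.

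**The concern.** The section gives all four inputs and the output, so it can be checked, and 60 is far too few for a two-arm comparison of means at 0.5. This is the only justification of the sample size, and it concerns the only primary outcome.

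The gap matters because of what is being compared. Both arms receive supervised exercise, with the same number and length of sessions, and the Introduction expects both to improve. A true difference of 0.5 SD would then be missed more often than found. A reader relying on the stated 80% could take a non-significant result as good evidence that motor control training has no moderate advantage, and the Discussion says the findings are meant to help clinicians choose a programme.

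**Working it through.** **Inputs from the Protocol:** power 0.80, alpha 0.05, effect size 0.5, dropout 15%, 60 recruited, 30 per arm. Evaluable: 60 × 0.85 = 51, or 25.5 per arm on average.

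**Assumptions where the Protocol is silent:** 0.5 is Cohen's d, the difference in means divided by the SD, and the test is a two-sided two-sample t-test. Two-sided fits the planned 95% intervals. Other readings are tried in steps 4 and 5.

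**1. Attempt to reproduce 60.** The normal approximation gives n per arm = 2(1.960 + 0.842)² / 0.5² = 62.8, so 63. The exact noncentral t calculation gives 79.5% power at 63 per arm and 80.1% at 64, so 64 per arm. The total is 128 evaluable, and 128 / 0.85 = 150.6, so 151 recruited (152 with equal arms). The Protocol has 60, so its figure does not reproduce.

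**2. Power that 60 gives at d = 0.5.** The noncentrality is d√(n/2), with 2n − 2 degrees of freedom.
- 51 evaluable: 0.5 × √(25.5/2) = 1.785, 49 df, critical t 2.010; power 41.7%.
- All 60 evaluable: 0.5 × √(30/2) = 1.936, 58 df, critical t 2.002; power 47.8%.

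**3. Effect detectable with 80% power.** Solving the same formula for d gives 0.80 with 51 evaluable and 0.74 with 60. In the forward direction, d = 0.8 needs 26 per arm, 52 in all. Then 52 × 1.15 = 59.8, which rounds to 60; the correct inflation, 52 / 0.85 = 61.2, gives 62.

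**4. Other readings of the stated inputs.**

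| Reading | Needed before dropout | After 15% dropout | Gives 60? |
|---|---|---|---|
| One-sided t-test, d = 0.5 | 51 per arm, 102 in all | 120 | No (power 54.6% at 51 evaluable) |
| One-way ANOVA, f = 0.5 | 34 in all | 40 | No |
| Paired t-test, d = 0.5 | 34 | 40 | No |
| Repeated measures, between factor, f = 0.5, 2 or 3 times, correlation 0 or 0.5 | 14 to 26 in all | at most 31 (26 / 0.85 = 30.6) | No |
| Repeated measures, group by time, f = 0.5, same settings | 10 to 18 in all | at most 22 (18 / 0.85 = 21.2) | No |

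**5. Credit for the baseline covariate.** Adjustment divides the residual SD by enough to turn d into d / √(1 − r²), where r is the correlation between baseline and week-8 pain. The Protocol gives no r, so a range is shown for 51 evaluable, two-sided.

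| Assumed r | Effective d | Power at d = 0.5 |
|---|---|---|
| 0 | 0.50 | 42% |
| 0.3 | 0.52 | 45% |
| 0.5 | 0.58 | 52% |
| 0.7 | 0.70 | 69% |
| 0.78 | 0.80 | 80% |

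**6. What a null result could exclude.** Without adjustment, the 95% interval with 51 evaluable has half-width 2.010 × √(2/25.5) = 0.56 SD. Even an observed difference of exactly zero would leave 0.5 SD inside the interval.

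**The case against.** The strongest reply is that the 42% is conditional. The section states neither Cohen's d, nor a two-sided test, nor an unadjusted analysis. G*Power uses f for ANOVA-type tests, and if 0.5 is f, then 60 women are more than enough: power is about 94% with 51 evaluable. On this view the text shows only that the number cannot be reproduced, and the shortfall appears once d is assumed.

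It is also fair that the origin of 60 is unknown. An effect of 0.8 fits through 52 × 1.15. So does a slip in which a one-sided per-arm number, 51 / 0.85 = 60, was taken as the total. Repeated-measures settings with f = 0.25 can be tuned to reach 60 as well: at correlation 0.22 with two time points, 52 are needed, again giving 59.8. Finally, 95% intervals are already planned.

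The point about origin stands, and the sponsor should look up the original calculation. The rest does not rescue the text. For one continuous outcome compared between two arms at one main time point, d is the natural meaning. Reading 0.5 as f means d = 1.0, a very large difference between two active programmes, and gives 34 rather than 60. The f = 0.25 fits use an effect size the Protocol does not state. That 51 evaluable women give 80% power at d = 0.80 is true however 60 was reached. Planned intervals help interpretation but do not correct the power claim.

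**Conclusion.** The concern holds. No standard reading of the stated inputs that was tried gives 60. On the natural reading the trial has about 42% power at an effect of 0.5, roughly half of what is claimed, and the recruitment needed for 80% is about 151, two and a half times the plan (151 / 60 = 2.5). The figure rests on Cohen's d, a two-sided 5% test, 51 evaluable women and no baseline adjustment. Relaxing one of these at a time gives 48% with no dropout, 55% one-sided and 52% with an assumed r of 0.5. Only an assumed r of about 0.78 or more restores 80% two-sided, and the Protocol neither states nor uses such a value. As planned, the trial is sized for a difference of about 0.8 SD. The paragraph must be corrected.

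**What to change.** Rewrite the sample size paragraph and keep 60 women. After checking the original G*Power entry, state the test, the type of effect size and the sidedness, and inflate for dropout by N / (1 − 0.15). Suggested wording:

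> Sixty women (about 51 evaluable after 15% dropout) give 80% power, at two-sided alpha 0.05 in a two-sample comparison of mean pain at 8 weeks, for a standardised difference (Cohen's d) of about 0.8. Power for a difference of 0.5 is about 42%, or about 52% with baseline adjustment if the correlation between baseline and week-8 pain is 0.5 (assumed). A non-significant result will not be taken to exclude a moderate effect and will be interpreted from the 95% confidence interval.

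The cost is one paragraph and a less favourable power statement, with no extra patients and no change of design. If the check shows that 0.5 is the difference the trial must be able to detect, this wording does not supply the missing power; recruitment of about 151 would be needed, or a documented baseline correlation high enough to reduce that number.
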